### Secondary outcomes

Secondary outcomes consist of functional performance-based tests and rating scales. The 6MWT measures the distance a patient can walk on flat ground within 6 min. To assess ROM, the patient is required to lie flat on a bed or examination table, while the examiner measures the maximum angles of flexion and extension using a standard angle measuring instrument. VAS involves the use of a 10-cm-long line with anchor points at the ends, enabling the patient to self-assess and rate the intensity of pain. The 6MWT, ROM, and VAS can effectively reflect the knee function. In addition, the KSS and WOMAC provide a comprehensive evaluation of the patient's overall condition, including knee joint function, daily living ability, and quality of life.

### Data analysis

The study schedule is depicted in Table 1. Data of all patients are recorded in Excel format and imported into SPSS (version 26.0; Armonk, New York, USA) for statistical analysis. To minimize bias due to missing data, intention-to-treat analyses and multiple imputation methods are employed. Descriptive statistics of measurement data are presented as mean ± standard deviation, while counting data are expressed as rate and composition ratio. Continuous variables are subjected to Student's *T* test if they meet the normal distribution, and Wilcoxon rank sum test is used otherwise. Categorical variables are tested using the chi-square test or Fisher's exact test. Secondary analyses are adjusted for baseline characteristics using analysis of covariance (ANCOVA). This study involves conducting multiple hypothesis tests, which undoubtedly increases the probability of Type I errors significantly. To control for family-wise error, Bonferroni corrections are adopted, resulting in a lowered adjusted *p* value of 0.002.

**Table 1 Tab1:** The patients’ schedule of trial enrollment, interventions, and assessment

Time point	Study period					
	Inpatient			Outpatient		
	Enrollment	Allocation	Pre-operation	2w	12w	24w
Enrollment						
Eligibility screen	×					
Informed consent	×					
Allocation		×				
Rehabilitation education			×			
Interventions						
Experimental group			×			
Control group			×			
Assessments						
Basal demographics and clinical data			×			
Cost					×	
Time					×	
6MWT						
ROM						
VAS						
KSS						
WOMAC						

“×” indicates the execution of the project according to the schedule

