### Sample size

Some researchers recommend that the sample size for each endpoint should be calculated separately, and the largest sample size should be chosen as the overall trial's sample size [30]. The study is designed with two primary outcome measures: cost and time. By calculation, the sample size calculated based on cost is larger. Therefore, it is selected as the total sample size. The type I error α is set at 0.05 (2-tailed analysis), and the test efficacy 1 − *β* at 0.9. Based on the combined standard deviation of 3987 in previously published literature [31], we estimate that the difference in cost between the two groups within 12 weeks after surgery is approximately 2000 RMB. Using the formula $$n = \frac{{2\left( {z_{\alpha } + z_{\beta } } \right)^{2} *\sigma^{2} }}{{\delta^{2} }}$$, we determined that 80 patients are needed in each group. Accounting for a dropout and loss to follow-up rate of 20–25%, we need to recruit a total of 200 patients.

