### Randomization and blinding

The 200 recruited patients are randomly assigned in a 1:1 ratio to either the experimental or control group using a computerized random number generator. Each patient is assigned a random number. Blinding is not possible due to the nature of the study, so neither patients nor physicians will be blinded to their group assignment. However, data analysts will not have access to any patient information other than their assigned number and will remain blinded during the statistical analysis of the collected data and presentation of results.

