### Outcome measures

At the time of hospitalization, all recruited patients complete baseline registration which includes gender, age, BMI (kg/m^2^), education level, medical insurance, dwelling place, comorbidities, and medications. Clinical assessments such as knee extension and flexion, KSS, WOMAC, and the American Society of Anesthesiologists (ASA) physical status classification are also completed. At 2 weeks, 12 weeks, and 24 weeks after discharge, 6WMT, ROM, VAS, KSS, and WOMAC of patients are evaluated. The cost and time are calculated at 12 weeks after discharge.

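### The main comparison of cost and time is unadjusted, which is valid but gives up precision that baseline data already collected could supply

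*Protocol article*

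**What the plan says.** All references are to the protocol article.

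- **Main test (Data analysis).** Continuous variables are compared by Student's t test if normally distributed, otherwise by the Wilcoxon rank sum test. No covariates enter. Cost (RMB) and time (hours) are continuous, so this is the test they receive.
- **Adjustment (Data analysis).** "Secondary analyses are adjusted for baseline characteristics using analysis of covariance (ANCOVA"). The section does not say which analyses count as secondary, which outcomes they cover or which covariates are used.
- **Baseline data (Outcome measures).** Age is recorded at admission, as are "education level, medical insurance, dwelling place, comorbidities, and medications". Knee extension and flexion, KSS and WOMAC are also assessed then.
- **Primary outcome.** The cost total over 12 weeks after discharge includes transportation, consultations, mobility aids, imaging and medications.
- **Allocation (Randomization and blinding).** Patients are "randomly assigned in a 1:1 ratio to either the experimental or control group using a computerized random number generator". No stratification factor is named.
- **Sample size.** The calculation is also unadjusted. It uses a raw SD ("Based on the combined standard deviation of 3987 in previously published literature") and concludes that "we determined that 80 patients are needed in each group".

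**The concern.** A patient's spending and time on medical visits plausibly depend on how far away they live and on what else is wrong with them. The protocol points the same way: it counts transport in the primary cost, and its Discussion expects the device to help with geographical and transport barriers. Dwelling place and comorbidities are therefore natural covariates. Insurance may be one too, but the document does not say whether cost is recorded before or after reimbursement.

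Two things are at stake. First, variance in cost that these variables explain stays in the standard error when they are left out, so the confidence interval is wider than it need be. Second, if one arm happens to contain more rural patients, the unadjusted primary estimate carries that difference. A supporting ANCOVA might correct for it, but the headline result would not.

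**Working it through.** **Inputs from the Sample size section.** "The type I error α is set at 0.05 (2-tailed analysis"); "the test efficacy 1 − *β* at 0.9"; SD σ = 3987 RMB; difference δ = 2000 RMB ("the difference in cost between the two groups within 12 weeks after surgery is approximately 2000 RMB"); 80 per arm.

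**Step 1: the plan's own figure.**
n = 2(z₀.₉₇₅ + z₀.₉₀)² σ²/δ² = 2 × (1.960 + 1.282)² × 3987²/2000² = 83.5, so 84 per arm against the stated 80. The stated figure is not reproduced exactly. That is a separate matter. Here it only sets the starting power.

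**Step 2: unadjusted power at 80 per arm.**
SE = 3987 × √(2/80) = 630 RMB. δ/SE = 2000/630.4 = 3.173. Power = Φ(3.173 − 1.960) = Φ(1.213) = 88.7%.

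**Step 3: effect of adjustment.** If the covariates explain a share R² of the variance in cost, the SE is multiplied by √(1 − R²). The documents give no R², so the range below is an assumption.

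| Assumed R² | SE (RMB) | δ/SE | Power at 0.05 | n per arm for 90% power |
|---|---|---|---|---|
| 0 | 630 | 3.173 | 88.7% | 84 |
| 0.05 | 614 | 3.255 | 90.2% | 80 |
| 0.10 | 598 | 3.344 | 91.7% | 76 |
| 0.20 | 564 | 3.547 | 94.4% | 67 |
| 0.30 | 527 | 3.792 | 96.7% | 59 |

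The SE falls by 3% at R² = 0.05 and by 16% at R² = 0.30. The 95% CI half-width falls from 1.96 × 630.4 = 1236 RMB to 1204 RMB and 1034 RMB respectively.

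**Step 4: if the Bonferroni threshold of 0.002 applied to cost.** The Data analysis section does not say whether it does. If it did, power at 80 per arm would be 53% unadjusted, and 57%, 60%, 68% and 76% at R² of 0.05, 0.10, 0.20 and 0.30.

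**Step 5: how large a chance imbalance could be.** Take a binary covariate with 50% prevalence (assumed) and allocation without stratification. With 80 per arm, the difference in share between arms has SE √(0.25 × 2/80) = 7.9 percentage points. A gap of 10 points or more then has a probability of about 21%. With 100 per arm, the SE is 7.1 points and the 95% range is ±13.9 points. The shift in the cost estimate is the gap times the cost difference between the two categories, so a 10-point gap moves it by one tenth of that difference. The documents do not give that cost difference, so the shift cannot be put in RMB.

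The steps cover cost only. No SD or target difference is stated for time. The figures are for a comparison of means, not for the Wilcoxon test.

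**The case against.** The strongest reply is that nothing here is wrong. An unadjusted two-sample comparison in a randomised trial is unbiased over randomisation and keeps its type I error. Its standard error already allows for chance imbalance. The sample size formula is unadjusted too, so design and analysis agree. All of this stands. A reader might infer that the primary test is invalid or biased, and the documents do not support that.

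Three other stronger readings also fail:

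- **That the recorded variables are strong predictors.** The document gives no association between any baseline variable and cost or time. Dwelling place and comorbidities are plausible predictors and insurance is a possible one. At R² = 0.05 the gain in power is only 1.5 points.
- **That cost and time are never adjusted, and that ROM, KSS and WOMAC also ignore their baseline values.** The undefined term has two natural readings. If it means analyses of the secondary outcomes, those three scales are adjusted. If it means supporting analyses of all outcomes, cost and time receive an adjusted analysis. Each reading removes one of the two complaints. On both, the headline test of cost and time is unadjusted.
- **That allocation is known to be unbalanced on these factors.** The article names no stratification, but it does not say there is none, and a condensed article may leave that out.

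It can also be said that covariate lists belong in an analysis plan that is not shown. That is fair for the list itself. The choice between an unadjusted and an adjusted primary test, however, is made in this document.

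**Conclusion.** The point holds as a missed gain in efficiency, not as an error. As written, the main test of both primary outcomes leaves out baseline variables that plausibly predict cost and are already in the data set. At 80 per arm and two-sided 0.05, power for cost is 88.7% unadjusted. Adjustment would lift it to between 90.2% and 96.7% for R² from 0.05 to 0.30. Even the lowest of these values would bring power back above the planned 90%.

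The size rests on the assumed R², on the plan's own SD and difference, and on a normal approximation for the difference in means. If the covariates prove weakly prognostic, the gain is small. Chance imbalance is left uncorrected in the primary estimate. Whether a supporting analysis corrects it cannot be told from the text.

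**What to change.** 1. Make the primary analysis of cost, and separately of time, a covariate-adjusted mean difference. Use a linear model with arm, dwelling place, insurance type, age and comorbidity, and a robust or bootstrap confidence interval because such data may be skewed. Fix the covariates and their coding before the analysts are unblinded.
2. Keep the unadjusted comparison as a sensitivity analysis.
3. Define which analyses the ANCOVA sentence covers. State that for ROM, KSS and WOMAC the ANCOVA uses each outcome's own baseline value and is their main analysis.

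**Cost.** Wording and a little more analysis work. The covariates are already collected, and the Trial status section says that the trial has not begun. The sample size need not change. The main downside is that the gain may be slight if the covariates explain little of the variance.

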Wearable micro-sensing devices have become commonplace in the sports industry for real-time performance analysis of athletes [23, 24]. For instance, in the case of total hip arthroplasty and cardiovascular risk factors, accelerometry can be employed to monitor physical activity levels and estimate calories and energy expenditure by tracking movement patterns, including steps taken and distance traveled [25–27]. However, their potential use in healthcare has yet to be fully realized [28]. The number of studies on wearable motion sensors has grown in recent years, with many focused on knee replacements, providing additional information to clinical metrics [29]. This study aims to evaluate the cost, time savings and effectiveness of an innovative treatment approach using a new, simple monitoring device in conjunction with a mobile phone app to guide patient rehabilitation exercise. We hypothesize that patients in the experimental group would exhibit improved short-term functional outcomes and experience cost and time savings compared to patients in the control group.

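### Optional improvement: Holm's step-down procedure gives the same 5% family-wise error bound as the plan's fixed Bonferroni cut-off and never rejects less, for a small, conditional gain in power

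*Protocol article*

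**What the plan says.** The Data analysis section of the protocol article recognises that many tests will be run. It says "To control for family-wise error, Bonferroni corrections are adopted", "resulting in a lowered adjusted *p* value of 0.002". No step-down version is named and only one threshold is given, so the text reads as single-step Bonferroni: every p value is compared with the same 0.002. The section does not state the number of tests, nor whether the two primary outcomes (cost and time) are in the same family as the secondary outcomes.

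The functional tests come from the Outcome measures section: "At 2 weeks, 12 weeks, and 24 weeks after discharge, 6WMT, ROM, VAS, KSS, and WOMAC of patients are evaluated". Five measures at three visits make 15 comparisons. They are secondary outcomes, but function is part of the trial hypothesis in the Background, which expects that "patients in the experimental group would exhibit improved short-term functional outcomes".

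The Sample size section is built on cost alone, at an unadjusted two-sided level: "The type I error α is set at 0.05 (2-tailed analysis"), with "test efficacy 1 − *β* at 0.9". It claims no power for any functional outcome.

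**The concern.** The stated aim is control of the family-wise error. If a second method meets that aim with the same bound, needs no extra assumption and never rejects less, the first method has little to recommend it apart from simplicity and easier simultaneous confidence intervals. Holm's procedure stands in that relation to Bonferroni.

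What is at stake is a true functional difference whose p value falls between the fixed cut-off and the larger threshold Holm would have reached. The plan would call such a difference non-significant without gaining any error protection. How often this happens depends on how many functional differences are real and how large they are.

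**Working it through.** **1. The plan's cut-off.** 0.05/m = 0.002 gives m = 0.05/0.002 = 25. The article does not state this number. The outcomes it lists give 2 + 15 = 17 tests (0.05/17 = 0.0029), or 2 + 18 = 20 if flexion and extension are counted separately (0.05/20 = 0.0025). So 0.002 is exact for 25 tests but cannot be confirmed from the listed outcomes. I use m = 25 as the plan's own rule and m = 15 for a family of functional tests only.

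**2. Why Holm dominates.** Order the p values and compare them in turn with 0.05/m, 0.05/(m − 1), ..., 0.05, stopping at the first failure.
- *Nothing is lost.* Every Holm threshold is at least 0.05/m, so any p value at or below 0.05/m is also rejected by Holm.
- *The error bound is the same.* Let m₀ be the number of true null hypotheses. When the first of them is rejected, at least m₀ hypotheses are still in play, so its p value is at most 0.05/m₀. By the union bound this has probability at most m₀ × 0.05/m₀ = 0.05, whatever the correlation.

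Simulation agrees (40,000 trials per setting, m = 17 or 25, correlation 0 or 0.5). Holm's family-wise error was at most 0.049, and it kept every Bonferroni rejection in every replicate.

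**3. Inputs for the size of the gain.**
- From the article: 80 per group, two-sided tests, overall level 0.05, cut-off 0.002.
- Assumed, because the article gives nothing for function: a standardised difference of 0.5 as the main case; correlation 0.6 between visits of one scale and 0.35 between scales.
- For m = 25, the ten tests outside the 15 functional ones are treated as never rejected.

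**4. Bonferroni baseline by formula.** The mean of the test statistic is d√(n/2) = 0.5 × √40 = 3.162.
- m = 25: the two-sided critical value at 0.002 is 3.090, so power is Φ(3.162 − 3.090) = 52.9%.
- m = 15: the critical value at 0.05/15 = 0.0033 is 2.935, so power is Φ(3.162 − 2.935) = 59.0%.

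**5. Gain from Holm by simulation.** Average power per true functional difference:

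| Family | Real differences (0.5 SD) | Bonferroni to Holm | Gain |
|---|---|---|---|
| m = 25 | 5 of the 15 functional | from about 53% | about 1 point |
| m = 25 | 9 of the 15 functional | from about 53% | about 2 points |
| m = 25 | all 15 functional | 52.6% to 57.2% | about 5 points |
| m = 15 | 5 of 15 | from about 59% | about 2 points |
| m = 15 | 9 of 15 | 59.4% to 64.2% | about 5 points |
| m = 15 | all 15 | 58.9% to 71.5% | about 13 points |

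At 0.4 SD with m = 15 and all real, the change is 34.3% to 42.7%.

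The pattern follows from the thresholds. With m = 25, after 14 rejections the next threshold is only 0.05/11 = 0.0045. With m = 15, after 14 rejections it is 0.05. A large gain needs nearly the whole family to be real. In a separate run with all 25 tests real at 0.5 SD, power went from 52.9% to 65.0%; with only three real it went from 53.1% to 53.6%.

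**6. What does not change.** Holm's first threshold is 0.05/m, the same as Bonferroni's, so the chance of at least one rejection in the family is identical.

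**7. Cost.** The inputs are a "combined standard deviation of 3987 in previously published literature" and the assumption that "the difference in cost between the two groups within 12 weeks after surgery is approximately 2000 RMB". At 80 per group, power for cost is 88.7% at 0.05 and 53.3% at 0.002. Under Holm with m = 25, cost still faces 0.002 unless other tests have been rejected first, so this gap remains.

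**The case against.** The strongest reply is that this is a choice between two valid methods. The plan recognises multiplicity, names a correction and gives the cut-off, and Bonferroni controls the family-wise error as claimed. Functional outcomes are secondary and no power was promised for them, so no design commitment is broken. All of that stands, and it is why this point is not graded as an error.

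A reader might also infer that the plan gives up some 13 points of power for function (59% to 72%). The article does not support that as the expected loss. It needs a family of exactly 15 tests, all of them real, each at 0.5 SD, whereas the plan's cut-off implies 25. Nor does the hypothesis say how many scales or visits should differ. Other parts of the article point to few true differences. The Background and Discussion report that supervised exercise brings no additional functional benefit, and the devices are handed back at week 12, so an effect at all three visits is not the natural base case. With few real effects the gain is about 1 point.

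What the reply does not remove is the dominance itself. At the same error bound Holm can only match or exceed Bonferroni. The usual reason to stay with Bonferroni is simple simultaneous confidence intervals, and the article does not mention any. Since the full protocol and analysis plan are not shown, that silence is weak evidence.

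**Conclusion.** The point holds as an optional, cheap improvement and not as an error. Single-step Bonferroni at 0.002 is valid but dominated by Holm for the aim the plan states.

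At the plan's cut-off the gain in average power per true functional difference is about 1 to 5 points. It is larger, up to about 13 points at 0.5 SD, only when every test in the family is a true difference, as with the 15 functional tests alone. These sizes rest on assumed effects, assumed correlations and 80 analysed patients per group. The dominance rests on none of these assumptions.

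Two stronger readings should be resisted. The plan does not fail to control the family-wise error. And Holm would not repair the separate mismatch between a sample size set at 0.05 and testing at 0.002 in an undefined family: its first threshold is the same, and the chance of any rejection is unchanged. That mismatch needs its own resolution.

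**What to change.** In the Data analysis section, replace the fixed cut-off by Holm's step-down procedure within whichever test family is kept. State m, order the p values, compare them with 0.05/m, 0.05/(m − 1), ..., 0.05, and stop at the first failure. Report Holm-adjusted p values: for the i-th smallest, the largest value of (m − j + 1) × p₍ⱼ₎ over j ≤ i, capped at 1.

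This takes one sentence in the plan, no extra patients or data, and simple arithmetic on p values that will be computed anyway. It should be fixed before outcomes are compared by group; the Trial status section says the trial had not begun. The one real downside is that simultaneous confidence intervals matching Holm are less simple than Bonferroni intervals. If such intervals are wanted, keeping Bonferroni is a defensible choice, and the plan should give that as the reason.

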**Discussion:**

We should encourage the adoption of novel, easy-to-use, supervised devices if they prove to be beneficial for patients in terms of cost, time, and effectiveness after TKA. This type of device is particularly important for people in remote rural areas, those with limited financial resources, and those who are reluctant to return to hospitals for follow-up care.

*Trial registration* Chinese Clinical Trial Registry ChiCTR2300068418. Registered on 17 February 2023.

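### Cost is sized at two-sided 0.05, but the analysis section's single 0.002 threshold does not exempt the primaries; on the plain reading, power for cost is about 53%, not 90%

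*Protocol article*

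**What the plan says.** The Sample size section of the protocol article names two primary outcomes, cost and time, and takes cost as the one needing more patients. Its design values are:

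- Significance level: "The type I error α is set at 0.05 (2-tailed analysis".
- Power: "the test efficacy 1 − *β* at 0.9".
- Variability: "Based on the combined standard deviation of 3987 in previously published literature".
- Effect: "the difference in cost between the two groups within 12 weeks after surgery is approximately 2000 RMB".
- Result: "80 patients are needed in each group", raised to 200 in total for a "dropout and loss to follow-up rate of 20–25" per cent.

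The Data analysis section observes that the study makes many hypothesis tests and that this inflates the type I error. It continues: "To control for family-wise error, Bonferroni corrections are adopted", and gives 0.002 as the resulting threshold. It does not list the tests that share the correction. It sets no level, order or exemption for cost and time.

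**The concern.** The two sections give different error rates, and nothing says which one governs the primary test. The sample size assumes that cost is judged at 0.05. The only threshold in the analysis section is 25 times smaller. If that threshold applies to cost, the primary outcomes pay for every functional score at 2, 12 and 24 weeks, which 5% control of the primary claim does not require.

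The trial's main question would then be answered by a test with far less power than the protocol states. A real saving of the planned size would be missed nearly half the time, and a non-significant cost result would be hard to interpret. If the threshold is not meant for cost, readers cannot tell this from the text.

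**Working it through.** **Inputs**, all from Sample size: two-sided alpha 0.05, power 0.90, SD 3987 RMB, difference 2000 RMB, 80 per group. From Data analysis: threshold 0.002.

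**1. The plan's own figure.** The stated formula is n = 2(z_α + z_β)²σ²/δ². With z = 1.960 for two-sided 0.05 and 1.2816 for 90% power:

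n = 2 × (1.960 + 1.2816)² × (3987/2000)² = 83.5, so 84 per group.

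The stated 80 does not reproduce. A one-sided 0.05 gives 69, 85% power gives 72 and 80% power gives 63. The step from 80 to 200 does reproduce at 20% loss: 80/0.8 = 100 per group.

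**2. Which tests does 0.002 cover?** 0.05/0.002 = 25 tests if exact, or about 20 to 33 if 0.002 is rounded from between 0.0025 and 0.0015. Two primaries would give 0.025. Two primaries plus five secondary outcomes at three visits make 2 + 15 = 17 tests, or 0.05/17 = 0.0029. The family cannot be recovered from the text, but it must extend well beyond the two primaries.

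**3. Power for cost at 80 per group.** The noncentrality is (2000/3987) × √(80/2) = 3.173, and power = Φ(3.173 − z(1 − α/2)).

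| Two-sided level | z | Power |
|---|---|---|
| 0.05 | 1.960 | 88.7% |
| 0.025 | 2.241 | 82.4% |
| 0.05/17 = 0.0029 | 2.974 | 57.9% |
| 0.0025 | 3.023 | 55.9% |
| 0.002 | 3.090 | 53.3% |
| 0.0015 | 3.175 | 49.9% |

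The noncentral t gives 88.4%, 81.8% and 51.4% at 0.05, 0.025 and 0.002.

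**4. Splitting the shortfall.** From 90% to 88.7% is 1.3 points, due to 80 in place of 84. From 88.7% to 53.3% is 35.4 points, due to the threshold.

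**5. Other sample sizes at 0.002.** Power is 49.3% with 75 completers per group (25% loss). It would be 67.6% if all 100 per group gave full information. For 90% power, n = 2 × (3.090 + 1.2816)² × (3987/2000)² = 151.9, so 152 completers per group.

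**6. Primaries as their own family.** Under Holm, cost is rejected if its p value is at most 0.025, or if it is at most 0.05 and time has been rejected at 0.025. If time is independent of cost and has the same standardised effect, power for cost is 0.824 + 0.824 × (0.887 − 0.824) = 0.876. Simulated bivariate normal pairs with correlation 0 to 0.8 give about 86 to 88%. If time has no effect, power is about 82 to 83%.

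**The case against.** The strongest reply is that the article never says cost and time belong to the 0.002 family. The preceding sentences of Data analysis include one about secondary analyses, and Sample size fixes 0.05 for the test that sizes the trial. One could read the plan as primaries at 0.05 and everything else at 0.002. It is true that membership of the family is inferred. But the correction is introduced for the study's hypothesis tests as a whole, and no words exempt the primaries. Even on the other reading the text needs changing, because two primaries each tested at 0.05 would have no stated correction between them.

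It is also fair to say that flat Bonferroni is a valid procedure. The stated hypothesis in the Background includes better function alongside cost and time savings, and a flat family allows a functional claim even if cost fails. That stands, so the issue is the stated power and the unreconciled levels, not loss of error control.

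Three stronger readings go too far:

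- A reader might blame the 47% miss rate wholly on the secondary tests. About 11 points of it remain at 0.05, and about 18 at 0.025.
- A reader might take the abstract's remark about adopting devices "if they prove to be beneficial for patients in terms of cost, time, and effectiveness after TKA" as a rule that all outcomes must succeed, so that alpha need not be split. It is a general remark that also names effectiveness; it sets no decision rule.
- A reader might think that recounting the tests settles the matter. At 17 tests, power is still only about 58%.

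Finally, Data analysis allows a rank-sum test if cost is not normally distributed, so these normal-theory figures describe the plan's own sizing model and may differ from the power of the test actually used.

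**Conclusion.** The point holds on the plain reading of the Data analysis section, which is an inference from its wording and not an explicit statement. The 90% power in the Sample size section is not a property of the cost test as planned: at 0.002 with 80 per group it is about 53%, and 50 to 56% if 0.002 is rounded. The threshold accounts for about 35 points of the loss, and the difference between 80 and 84 per group for about 1.

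These figures rest on the protocol's SD and difference, the normal approximation, and 80 completers per group. The 86 to 88% under Holm further assumes that time has a similar standardised effect to cost, which the article does not state. No form of the fix restores 90% at 80 per group. This should be settled before unblinding, because it determines how the primary result will be judged.

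**What to change.** In **Data analysis**, replace the single 0.002 rule with two families:

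1. Test cost and time together at an overall two-sided 5% by Holm: 0.025 for the smaller p value and, if that is rejected, 0.05 for the other.
2. Apply the correction for the secondary outcomes in a separate family, and list the tests in it.

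If family-wise control across both families is wanted, open the secondary family at 5% only when both primaries are rejected, or pass on only the alpha that the primaries release. Otherwise report the secondaries as estimates with confidence intervals. The gate must be this explicit. If one primary rejection opened a fresh 5% family, and the other primary and all the secondaries were null, family-wise error could reach 1 − 0.95² = 9.75% under independence.

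In **Sample size**, state the alpha at which cost is tested and the power it gives: about 82% at 0.025 with 80 per group, and about 86 to 88% under Holm with the assumption about time stated. Correct 80 to 84 for the formula at 0.05, or say what 80 gives.

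If 0.002 was always meant for the secondaries only, say so and still give cost and time a level.

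The cost is about one paragraph in the analysis section and a sentence in the sample size section, before unblinding, with no new patients or data. The downside is that, with the gate, secondary p values become descriptive if it is not met, including those for the functional outcomes named in the hypothesis.

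### Cost is sized at two-sided alpha 0.05, but the analysis section sets a threshold of 0.002 without exempting the primaries; read as written, power is about 51–53%, not 90%

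*Protocol article*

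**What the plan says.** In the Protocol article, the Sample size section states that "The study is designed with two primary outcome measures: cost and time". It calculates a size for each, finds the one for cost larger, and adopts it. For that calculation, "The type I error α is set at 0.05 (2-tailed analysis") and power is fixed by "the test efficacy 1 − *β* at 0.9". The planning values are an SD of 3987, taken from published literature, and the estimate that "the difference in cost between the two groups within 12 weeks after surgery is approximately 2000 RMB". The result is that "we determined that 80 patients are needed in each group". Recruitment follows from this: "Accounting for a dropout and loss to follow-up rate of 20–25%, we need to recruit a total of 200 patients". No multiplicity adjustment enters the calculation.

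The Data analysis section first remarks that the study carries out multiple hypothesis tests and that this raises the type I error. It then states that, to control family-wise error, "Bonferroni corrections are adopted, resulting in a lowered adjusted *p* value of 0.002". It does not list the tests in the family, limit the correction to secondary outcomes, or give cost and time an alpha of their own. The same section specifies intention-to-treat analysis with multiple imputation, and a t-test for normally distributed continuous variables with the Wilcoxon rank sum test otherwise.

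**The concern.** Stated power belongs to a particular test at a particular significance level. Here the 90% belongs to a test of cost at 0.05, while the only decision threshold in the analysis section is 0.002. Cost and time are among the study's hypothesis tests, so on a plain reading the threshold covers them.

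Two things are at stake. First, if 0.002 governs, the trial has far less chance of declaring the assumed 2000 RMB saving than its readers are told. Second, the primary conclusion is not fixed in advance. A cost result with p = 0.01 would be positive at the alpha in the Sample size section and negative at the threshold in the Data analysis section, and the article does not say which applies.

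**Working it through.** **Inputs.** From the Sample size section: difference δ = 2000 RMB, SD σ = 3987, two-sided alpha 0.05, power 0.90, 80 evaluable per arm, 200 recruited, 20–25% loss. From Randomization and blinding: 1:1 allocation, so 100 per arm. From Data analysis: threshold 0.002.

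**Step 1: the plan's own figure.** The protocol's formula is n = 2(z_α + z_β)²σ²/δ². With z = 1.960 and 1.282:

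n = 2 × (3.2415)² × (3987/2000)² = 2 × 10.507 × 3.974 = 83.5, so 84 per arm.

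The stated 80 is slightly low and gives 88.7% power at 0.05. That gap is small and is not the point here. For loss, 80/(1 − 0.20) = 100 per arm agrees with 200 recruited. At 25% loss, 100 × 0.75 leaves 75 per arm.

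**Step 2: power at each alpha.** The standardised difference is δ/(σ√(2/n)):

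- n = 75: 3.072
- n = 80: 3.173
- n = 100: 3.547

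Power ≈ Φ(standardised difference − z), with two-sided critical values 1.960 (alpha 0.05), 2.241 (0.025) and 3.090 (0.002). For n = 80:

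- alpha 0.05: Φ(3.173 − 1.960) = 88.7%
- alpha 0.025: Φ(3.173 − 2.241) = 82.4%
- alpha 0.002: Φ(3.173 − 3.090) = 53.3%

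Normal approximation / noncentral t:

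| Per arm | alpha 0.05 | alpha 0.025 | alpha 0.002 |
|---|---|---|---|
| 75 (25% loss) | 86.7% / 86.3% | 79.7% / 78.9% | 49.3% / 47.3% |
| 80 (planned) | 88.7% / 88.4% | 82.4% / 81.8% | 53.3% / 51.4% |
| 100 (no information lost) | 94.4% / 94.2% | 90.4% / 90.0% | 67.6% / 66.1% |

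The last row is a ceiling. Multiple imputation keeps all randomised patients in the analysis, but does not by itself restore the information lost with missing outcomes.

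**Step 3: what 0.002 would require.** For 90% power, n = 2 × (3.090 + 1.282)² × 3.974 = 151.9, so 152 evaluable per arm. With 80 per arm, the difference detectable with 90% power is (3.090 + 1.282) × 3987 × √(2/80) ≈ 2756 RMB, against the 2000 RMB assumed.

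**The case against.** The strongest reply is that the scope of 0.002 is inferred. The article names no family of tests, and the Bonferroni sentences come directly after one on adjusted secondary analyses, so the sponsor may have meant the threshold for secondary outcomes only. This stands in part. A reader might infer that the primaries will certainly be judged at 0.002 and that 52% is the trial's true power. The text supports only the weaker statement that 0.002, as written, appears to cover them. The alternative reading still leaves a gap: the article would have to say so and give the primaries an alpha. Bonferroni over the two primaries starts at 0.025 and gives about 82% with 80 per arm. Testing each at an unadjusted 0.05 would not control family-wise error if success on either suffices, and the article does not say that both are required.

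A reader might also infer that 0.002 is the wrong divisor, because 0.05/25 = 0.002 and the listed outcomes and visits suggest fewer tests. The documents do not establish this. No count is stated; anything from 21 to 33 tests rounds to 0.002 (0.05/21 = 0.0024, 0.05/33 = 0.0015); and a count of outcomes by visits omits the covariance-adjusted and categorical analyses that the section also names. Nor is a single strict Bonferroni family invalid. It is conservative, and the fault is only that the sample size does not reflect it.

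Finally, costs may not be normally distributed, in which case the Wilcoxon test applies. Its power cannot be derived from a mean difference and an SD. This limits how exactly the shortfall can be stated, but the stated 90% rests on the same two-mean model.

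**Conclusion.** The concern holds in conditional form. The two sections use different alphas, and nothing in the article reconciles them. If 0.002 governs cost, power is about 51–53% at the planned 80 per arm. The range is 47–49% at the protocol's own 25% loss, up to a ceiling of 66–68% with full information from all 100 per arm. None of these is near 90%; at 80 per arm the shortfall against the stated figure is about 37 percentage points. The figures assume the protocol's difference and SD and a t-type comparison of means. They say nothing about power under the Wilcoxon fallback.

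**What to change.** State in both Sample size and Data analysis which alpha governs cost and time. Two wordings would reconcile the sections:

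- Limit the primary confirmatory family to cost and time, by Bonferroni or Holm starting at 0.025, and keep any stricter threshold for the secondary outcomes. Restate the power for cost as about 82% with 80 per arm. Under Holm this is a floor: if time is rejected first, cost is tested at 0.05 and its power rises to about 88–89%.
- Keep 0.002 for the primaries and restate the power for cost as about 52% with 80 per arm.

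Either costs wording only, and the price is a less favourable stated power. According to Trial status, this version predates the start of the trial, so the choice can be prespecified. Should the sponsor wish to hold 90% at 0.025, the same formula gives 2 × (2.241 + 1.282)² × 3.974 = 98.6, so 99 evaluable per arm, or 99/0.80 = 124 recruited per arm at 20% loss. That option would need more patients than the 200 planned.
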